#### The Oxford Participation and Activities Questionnaire

The Oxford Participation and Activities Questionnaire (Ox-PAQ) is a 23-item, generic, patient-reported outcome measure (Multimedia Appendix 11). Theoretically, it is grounded in the WHO International Classification of Functioning, Disability and Health [72]. It is primarily used in clinical trials to evaluate interventions targeted at improving or maintaining participation and activity. The measure demonstrates good reliability (Cronbach α=0.81-0.96) and validity and low levels of missing data across all 3 domains [73,74]. It equally demonstrates good convergent validity with the EuroQol-5D questionnaire [75].

#### Physical Activity Readiness Questionnaire

The Physical Activity Readiness Questionnaire (PAR-Q) was created by the British Columbia Ministry of Health and the Multidisciplinary Board on Exercise [76] (Multimedia Appendix 12). It is a simple self-screening tool that is used to plan an exercise program. The tool helps to determine the readiness for exercise as it reveals the safety or possible risk of exercising for an individual based on their health history, current symptoms, and risk factors. It is often used in clinical trials to ascertain readiness prior to enrollment [77].

#### Cardiorespiratory Measurements

Participants’ resting HR, systolic BP, and diastolic BP are monitored on the right arm [46,78] using an automated digital electronic BP monitor (Omron digital BP monitor, Model M2 Eco; Tokyo, Japan). These measurements are monitored between 7:00 am and 2:00 pm each test day.

#### Anthropometric Measurements

We assess participants’ physical characteristics (% body fat, weight in kg, height in meters, and BMI in kg/m^2^) according to a standardized anthropometric protocol [79,80].

#### Blood Sample Collection

Blood samples are collected using the venipuncture method. We collect venous blood samples both pre- and posttreatment between 8:00 am and 12:00 pm. We collect blood samples using a 5-mL syringe [48]. CD4 count tests are conducted within 12 hours, and samples for viral load are stored in a refrigerator at –80 °C until analysis [81].

#### Measurement of CD4 Count and Viral Load

Samples are analyzed by the UNTH ART clinic laboratory scientist. To control for the potential effects of rest, time of the day, season, ovulation, and vaccination, pre-exercise blood samples for quantifying CD4 count were drawn when patients arrived at the laboratory, after 60 minutes of rest [82]. To minimize diurnal variation, samples were collected between 8:00 am and 12:30 pm. We aimed to collect pre-exercise blood samples before the heavy rainfall season in June. In Nigeria, rainfall peaks in June [83] and is associated with increased opportunistic infections that influence CD4 count. After each sample was collected, we examined the tube for integrity before transporting to the testing center. All CD4 counts were measured within 12 hours of sample collection following the recommendation of the WHO [84-86].

### Data Management

Data are manually transcribed from paper forms into a Microsoft Excel spreadsheet and exported and secured to MicrOsiris 24.8. Data are verified through independent double data entry, where the principal investigator (data manager) and a data clerk both enter data. Consistency checks are performed during data entry, and warnings are displayed when needed.

Personal information such as contact number and identity number are collected and only used to reach participants when necessary and for possible access to participants’ hospital files. Data are handled confidentially and are not shared with a third party. Participants’ names do not appear in any data record except in a case of referral.

### Statistical Methods

Primary and secondary variables will be tested for normality and heterogeneity using Kolmogorov-Smirnov and Levene tests, respectively. We will compare the control group and exercise group using a 2-way analysis of variance with repeated measurements and Bonferroni correction. Primary outcome measures are cognitive performance, QoL, activity limitation, and participation. We will compute hazard ratios to evaluate the effect of the intervention over time. SPSS version 21 (IBM Corp, Armonk, NY) will be used.

We expect that potential confounding variables, not accounted for by randomization, may influence outcomes between the control and study groups. We will include potential confounding variables in appropriate analysis of covariance. Covariates include neurocognitive performance test scores (clinical rating algorithm), CD4 count (classified as <350 cells/µl or ≥350 cells/µl), viral load (classified as detectable [>400 copies/mL] or undetectable [<400 copies/mL]), age, sex, level of education, BMI, exercise adherence (classified as nonadherent [≤40%] or adherent [>40%]), adherence to ART since the intervention (classified as nonadherent [≤40%] or adherent [>40%]), ART regimen, ovulation, and vaccination status. Also, our findings will be included in an updated meta-analysis of the effects of exercise on cognition in people living with HIV to understand how the study outcome may drive existing associations. The initial meta-analysis was conducted by our team [43].

As per nonadherence to a study protocol, we will employ intention-to-treat analysis. Effort will be made to prevent missing data through cross-checking of the information obtained from participants. In case of missing data, we will explore patterns of missing and, where appropriate, multiple computation will be executed using SPSS version 21.

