### Study Outcomes

The primary outcomes include neurocognitive performance, prevalence of HAND, viral load, and CD4 count. The secondary outcomes include maximum oxygen uptake (VO_2_), QoL, activity limitation, and participation restriction. Potential confounding variables include age, sex, level of education, vaccination, history of virologic failure, level of ART adherence, exercise adherence, ART regimen, ovulation status, history of recent vaccination, and seasonality. These variables will be measured at baseline, after 12 weeks, and 3 months after the intervention. Their change will be measured over time. Aggregation parameters will include proportion, mean, or median depending on how the data are distributed.

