### Sample Size

An estimated sample size of 68 (34 in each group) will have 90% power to detect a difference in means of 13.4 (the difference between a Group 1 mean, µ_1_, of 56 and a Group 2 mean, µ_2_, of 42.6) assuming that the common SD is 16.67 using a 2-group *t* test with a 5% 2-sided significance level.

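### Holm's step-down correction could replace Bonferroni for the group comparisons: a cheap efficiency gain whose size depends on the family and on how many effects are real, not the repair of an error

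*Protocol article*

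**What the plan says.** The correction appears once, in Statistical Methods: "We will compare the control group and exercise group using a 2-way analysis of variance with repeated measurements and Bonferroni correction". No family and no divisor are given. The next sentence there reads: "Primary outcome measures are cognitive performance, QoL, activity limitation, and participation".

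Study Outcomes gives a different list of four: "The primary outcomes include neurocognitive performance, prevalence of HAND, viral load, and CD4 count". Only cognition is on both. It also sets the schedule: "These variables will be measured at baseline, after 12 weeks, and 3 months after the intervention". The correction could therefore run over outcomes, over the two follow-up visits, or over post hoc contrasts of the repeated-measures analysis.

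The Sample Size section plans for one comparison at a two-sided 5% level: "An estimated sample size of 68 (34 in each group) will have 90% power to detect a difference in means of 13.4", assuming the "common SD is 16.67". It does not say which outcome the difference belongs to, and it splits no alpha.

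**The concern.** Bonferroni without qualification means comparing every p-value in the family with 0.05/k. Holm's procedure gives the same 5% family-wise guarantee and uses larger thresholds after the first rejection. Choosing Bonferroni therefore leaves some rejections unused whenever more than one effect is real.

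With 34 per arm there is little power to spare once any correction applies. Real effects on some outcomes could go undeclared that Holm would have declared, and the set of findings would look patchier than the data require. The Results section reports that enrolment is complete and that analysis has not begun, so the testing procedure is easier to change than the sample size.

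**Working it through.** **Inputs.** From Sample Size: 34 per arm, difference 13.4, SD 16.67, two-sided 5%. From Trial Design: 1:1 allocation. My assumptions: the same standardised effect on every truly affected outcome, a common correlation between outcomes, independent variance estimates, t tests standing in for the repeated-measures contrasts, and no dropout. The article gives no between-outcome correlation and no second effect size.

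**1. The plan's own figure.** Standardised effect: 13.4/16.67 = 0.804. Noncentrality: 0.804/√(2/34) = 0.804/0.2425 = 3.31, on 66 degrees of freedom. Power is the probability that a noncentral t variable with these values exceeds the two-sided critical value in absolute size. At 0.05 this is 90.4% with 34 per arm and 89.5% with 33, so the planned 68 reproduces.

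**2. Bonferroni at the same sample size.** Same formula at 0.05/k:

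- k = 2 (0.025): 84.4%
- k = 3 (0.0167): 80.2%
- k = 4 (0.0125): 77.0%

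**3. Why Holm never rejects less.** Holm orders the p-values and compares them in turn with 0.05/k, 0.05/(k−1), …, 0.05, stopping at the first failure. Every threshold is at least 0.05/k, so every p-value at or below 0.05/k passes. If k₀ null hypotheses are true, a first false rejection requires the smallest of their p-values to be at or below 0.05/k₀. The chance of that is at most k₀ × 0.05/k₀ = 0.05, whatever the correlation. Holm's first step is the Bonferroni threshold, so one method rejects something exactly when the other does.

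**4. Size of the gain, family of four.** Simulation with 200,000 replicates per setting, effect 0.804 SD. Entries are Holm's average power per truly affected outcome; Bonferroni is 77.0% throughout. Gains are from unrounded values.

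| Real effects | Correlation 0 | 0.3 | 0.5 | 0.8 | Gain (points) |
|---|---|---|---|---|---|
| 4 | 87.5% | 86.2% | 85.4% | 84.0% | 10.5 to 7.0 |
| 3 | 82.9% | 82.2% | 81.9% | 81.1% | 5.9 to 4.2 |
| 2 | 79.6% | 79.3% | 79.1% | 78.9% | 2.6 to 1.9 |
| 1 | 77.1% | 77.1% | 77.0% | 76.9% | about 0.1 or less |

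With all four effects real, the chance of declaring all four rises from 35.1%, 44.2%, 50.0% and 60.2% to 65.0%, 69.4%, 72.7% and 78.0% at the four correlations. The chance of at least one rejection is the same under both methods in every row. With no real effect and correlation 0.3, the family-wise error is 4.7% for both.

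**5. Other families.** Two follow-up visits, both effects real: Holm 89.5%, 88.6% and 87.9% at correlation 0, 0.5 and 0.8, a gain of 5.1, 4.2 and 3.5 points. Three contrasts with two real: gain 3.5, 2.9 and 2.5 points.

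**6. Other effect sizes.** Family of four, all real, correlation 0.3: at 0.65 SD the gain is 9.9 points (54.8% to 64.7%), at 0.5 SD 6.0 points (31.4% to 37.4%), and at 0.3 SD 1.3 points (9.9% to 11.3%, from unrounded values). The gain holds up for a modest shortfall in effect and fades for a large one.

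**The case against.** The best objection is that this is a preference and not a fault. Bonferroni controls the family-wise error and comes with simple simultaneous confidence intervals that agree with its tests. Holm has no simple matching intervals. That stands: nothing in Statistical Methods is invalid on this point, and the change is an efficiency gain.

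Four stronger readings are tempting, and the documents do not support them.

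- A reader might infer that the plan loses 7 to 10 points on each primary outcome. That needs a correction over exactly four outcomes and a full 0.804 SD effect on all of them. The article states neither. Attached to a repeated-measures analysis, the correction may equally mean time-point or post hoc contrasts, and the sizing difference is tied to no named outcome.
- A reader might infer that the power is given up for nothing. What Bonferroni offers in return is the matching intervals.
- A reader might infer that the correction could turn the trial negative. It could not do so relative to Holm, because a trial with no Bonferroni rejection has no Holm rejection either. Only the number of further positive findings can change.
- A reader might infer that correlated outcomes favour Holm, since activity and participation are measured with one instrument: "The Oxford Participation and Activities Questionnaire (Ox-PAQ) is a 23-item, generic, patient-reported outcome measure". Holm does not exploit correlation, and its gain falls as correlation rises (10.5 to 7.0 points in the first row of the table).

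It is also fair to say that Holm cannot be applied until the family is declared. Bonferroni has the same gap, because its divisor is unknown too.

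**Conclusion.** The point holds as a low-cost improvement. Holm's advantage in rejections, at the same 5% family-wise level, does not depend on which family is meant. Only its size does.

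Across the effect patterns examined at 0.804 SD, for families of two to four tests, the gain per truly affected comparison runs from about 0 to 10.5 points. The top of that range is a best case, not an expected value. All of these figures rest on the assumptions listed with the inputs.

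Two firmer problems in the same place are separate and stay open under Holm. The primary-outcome lists in Study Outcomes and Statistical Methods conflict. The sample size was computed at an unadjusted 5%: a four-way Bonferroni split takes 90.4% down to 77.0%, and 46 per arm would be needed for 90%.

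**What to change.** In Statistical Methods, replace 'Bonferroni correction' with 'Holm (step-down Bonferroni) correction', applied to the group-comparison p-values of the family the correction is meant for, and name that family. Order the k p-values; compare the smallest with 0.05/k, the next with 0.05/(k−1), and so on; stop at the first that fails. Report Holm-adjusted p-values. Where simultaneous intervals are wanted, keep the Bonferroni intervals, and note in advance that a Holm-significant result may sit beside a Bonferroni interval that includes zero.

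The cost is one line of wording and a hand calculation on unadjusted p-values, with no added patients, visits or measurements. The amendment should be filed before group comparisons are run; the article's section on communicating amendments already covers changes to the analysis.

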**Methods:**

At least 68 patients diagnosed with HAND will be randomly placed into either an aerobic exercise group or control group. Patients in the aerobic exercise group will perform a moderate intensity workout on a stationary bicycle ergometer, 3 times a week for 12 weeks. We will measure the primary outcomes including neurocognitive performance, prevalence of HAND, viral load, and CD4 count. We will evaluate postexercise neurocognitive performance using reliable neuropsychological tests relevant to people living with HIV, in line with the Frascati criteria. We will assess secondary outcomes such as quality of life, activity limitation, and social participation using the World Health Organization Quality of Life (WHOQOL)-Brief, and the Oxford Participation and Activities questionnaire. We will use exploratory statistics to test the data for normality and homogeneity. We will analyze the effect of the exercise program on HAND using relative risk (RR) and absolute risk reduction (number needed to treat). Analysis of covariance will be run to estimate the effect of exercise on quality of life and activity and participation level.

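### The protocol gives two conflicting lists of primary outcomes; seven different outcomes are called primary somewhere, and the scope of the Bonferroni correction cannot be determined

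*Protocol article*

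**What the plan says.** Study Outcomes states: "The primary outcomes include neurocognitive performance, prevalence of HAND, viral load, and CD4 count". The Methods part of the Abstract gives the same four: "We will measure the primary outcomes including neurocognitive performance, prevalence of HAND, viral load, and CD4 count". Study Outcomes then adds: "The secondary outcomes include maximum oxygen uptake (VO_2_), QoL, activity limitation, and participation restriction". The Abstract agrees on the lower rank of three of these: "We will assess secondary outcomes such as quality of life, activity limitation, and social participation".

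Statistical Methods gives a different list: "Primary outcome measures are cognitive performance, QoL, activity limitation, and participation". The sentence before it plans a "2-way analysis of variance with repeated measurements and Bonferroni correction", without saying which tests the correction covers. The same section uses two of the primary outcomes from Study Outcomes as two-category covariates, CD4 count ("CD4 count (classified as <350 cells/µl or ≥350 cells/µl") and viral load, and also uses the neurocognitive score as a covariate.

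On timing, Study Outcomes says: "These variables will be measured at baseline, after 12 weeks, and 3 months after the intervention". Sample Size plans 68 participants (34 per group) for 90% power to detect one difference in means, 56 against 42.6 with SD 16.67, at a two-sided 5% level. It does not name the outcome to which those figures belong.

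**The concern.** The primary outcome determines what the trial may claim. Here three outcomes are secondary in one section and primary in another, and three primary outcomes of the first list are absent from the second. If cognition, CD4 count and viral load showed nothing but self-reported QoL improved, the trial could be reported as positive on a primary outcome, with this protocol cited in support. The opposite pattern could be cited just as well. The choice could then be made after the results are known.

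The conflict also leaves the error control and the power undefined. A correction over the primary outcomes needs a settled list of them, and the sample size was calculated for a single test at 5%.

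**Working it through.** **1. The lists side by side**

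| Outcome | Abstract and Study Outcomes | Statistical Methods |
|---|---|---|
| Cognitive performance | primary | primary (score also a covariate) |
| HAND prevalence | primary | not listed |
| Viral load | primary | not listed; two-category covariate |
| CD4 count | primary | not listed; two-category covariate |
| QoL | secondary | primary |
| Activity limitation | secondary | primary |
| Participation | secondary | primary |

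Outcomes called primary somewhere: 4 + 4 − 1 = 7.

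**2. The plan's own sample size**

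Inputs from Sample Size: difference 56 − 42.6 = 13.4; SD 16.67; two-sided alpha 0.05; power 90%. The standardised effect is 13.4 / 16.67 = 0.804.

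- Normal approximation: n per arm = 2 × [16.67 × (1.960 + 1.282) / 13.4]² = 32.5, so 33.
- Exact two-sample t test at 34 per arm: noncentrality 0.804 × √(34/2) = 3.314 on 66 degrees of freedom, critical value 1.997, power 90.4%. At 33 per arm the power is 89.5%, so 34 is the smallest adequate number.

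The stated 68 is reproduced, for one test at 5%.

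**3. If the Bonferroni correction does not cover the primary outcomes**

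With k tests, each at two-sided 5%, the chance of at least one false positive under independence is 1 − 0.95^k:

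- k = 4: 1 − 0.8145 = 18.5%
- k = 7: 1 − 0.6983 = 30.2%

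For jointly normal two-sided test statistics, correlation can only lower these figures. The documents give no correlations, so a common correlation ρ is assumed. The chance is then 1 − ∫ φ(u) [Φ((1.96 − √ρ·u)/√(1−ρ)) − Φ((−1.96 − √ρ·u)/√(1−ρ))]^k du.

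| Assumed ρ | 4 tests | 7 tests |
|---|---|---|
| 0 | 18.5% | 30.2% |
| 0.3 | about 17% | about 27% |
| 0.5 | 15.6% | 23.0% |
| 0.7 | about 13% | about 18% |

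Each outcome is counted as one test.

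**4. If the Bonferroni correction does cover them**

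Same effect of 0.804 on every outcome (an assumption), 34 per arm, exact t test:

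| Family | Alpha per test | Power per outcome | n per arm for 90% |
|---|---|---|---|
| 1 | 0.05 | 90.4% | 34 |
| 4 | 0.05/4 = 0.0125 | 77.0% | 46 |
| 7 | 0.05/7 = 0.00714 | 70.3% | 51 |

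So the stated power and an outcome-wide correction cannot both hold at 68 participants.

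**The case against.** The strongest reply is that multiplicity is addressed. A Bonferroni correction is planned, and the very next sentence lists the primary outcomes, so a reader may fairly take it to cover them. A detailed analysis plan, not shown here, would normally define the family, rank several primary outcomes and name the main time point. Having several primary outcomes is not in itself an error. Much of this stands. It would be wrong to infer that the plan has no multiplicity control, or that its false-positive rate is 30%. The rates in step 3 apply only if the correction turns out to mean something narrower, such as pairwise time contrasts within each analysis of variance.

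A reader might also infer that the trial offers seven outcomes at two follow-up times, that is 14 chances of success. The documents do not support that firmly. The sentence on measurement times directly follows the list of confounders, so its subject is ambiguous. Participant Timeline describes only assessments after the 12-week programme, and Blood Sample Collection only samples before and after treatment. Measurement of outcomes at three months is a likely reading but not a clear one, and a repeated-measures analysis would in any case examine the time points jointly.

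The outcomes are also linked. HAND status derives from the neurocognitive assessment, and activity and participation come from one questionnaire. The independent figures are therefore upper limits.

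None of this removes the contradiction. The word include in Study Outcomes might leave room for further primary outcomes, but QoL, activity limitation and participation are placed among the secondary outcomes there. Neither condensation into an article nor an unseen analysis plan makes two incompatible explicit lists compatible.

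**Conclusion.** The point holds as a contradiction in the current text that must be resolved before analysis. Seven outcomes are called primary somewhere, and only cognitive performance is primary throughout. Its consequence depends on what the Bonferroni correction covers:

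- If it does not cover the primary outcomes, the chance of at least one false positive is at most 18.5% (four tests) or 30.2% (seven), and 15.6% or 23.0% at an assumed correlation of 0.5.
- If it does, power per outcome at 68 participants is 77.0% or 70.3% and not 90.4%, assuming the same standardised effect on each outcome.

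The article does not say which case applies. The first set of figures is an unadjusted upper scenario, not a description of the plan. The sample size cannot decide which list governs, because its means are tied to no named outcome.

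**What to change.** Before data analysis:

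- Make the list of primary outcomes identical in the Abstract, Study Outcomes and Statistical Methods.
- In Sample Size, name the outcome to which the means of 56 and 42.6 and the SD of 16.67 refer, and make it the primary outcome or one of them.
- The simplest choice consistent with the sample size is one primary outcome, cognitive performance, at the end of the 12-week programme, with all others secondary. State how it is scored. The overall score from the clinical rating algorithm is in neither list, and Neuropsychological Screening reserves it for covariate analysis. If it is chosen, amend that section and remove the score from the covariates for that analysis.
- If the sponsor prefers several primary outcomes, state that the Bonferroni family is those outcomes and restate the power at the adjusted alpha.
- State whether outcomes are also measured three months after the intervention.
- Communicate the change by the route already set out in the section on protocol amendments.

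The article reports that analysis had not begun, so the cost is wording and an amendment. The downside is that some outcomes lose the primary label or, if several are kept, the stated power becomes less favourable.

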### Eligibility Criteria

We included patients if they met the following criteria: diagnosed with HAND and physically inactive (sedentary, <2 hours of exercise per week; ready to exercise upon assessment, not engaged in regular exercise for approximately 3 months before the study). Patients were excluded if they were older than 65 years; had uncontrolled hypertension (blood pressure [BP] ˃140/90 mm Hg), deafness, severe eye impairment, physical disability, history of traumatic brain injury, psychiatric illness, recent focal neurological deficit, active depression, alcohol or substance abuse, musculoskeletal injury, or acute illness capable of hampering exercise performance; pregnancy; or had angina pectoralis and/or shortness of breath at rest or during exercise. We excluded participants on cognition-enhancing drugs such as eugeroics, attention deficit/hyperactive disorder medications, and nootropic supplements.

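### Hazard ratios are planned although no outcome is a time to an event and no event is named, and the Abstract's risk measures for HAND are missing from Statistical Methods

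*Protocol article*

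**What the plan says.** Statistical Methods plans a two-way repeated-measures analysis of variance with Bonferroni correction, lists the primary outcomes, and then adds: "We will compute hazard ratios to evaluate the effect of the intervention over time". It does not say for which outcome or which event.

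The article lists its outcomes twice. Study Outcomes has: "The primary outcomes include neurocognitive performance, prevalence of HAND, viral load, and CD4 count". Its secondary outcomes are maximum oxygen uptake together with "QoL, activity limitation, and participation restriction". Statistical Methods has: "Primary outcome measures are cognitive performance, QoL, activity limitation, and participation".

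On who enters, Eligibility Criteria says: "We included patients if they met the following criteria: diagnosed with HAND and physically inactive". On when outcomes are taken, Study Outcomes says: "These variables will be measured at baseline, after 12 weeks, and 3 months after the intervention".

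The Abstract names other measures for the effect on HAND: "We will analyze the effect of the exercise program on HAND using relative risk (RR) and absolute risk reduction (number needed to treat". Statistical Methods mentions neither of them.

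**The concern.** A hazard ratio compares rates at which an event occurs over follow-up. It needs an event, a time origin and some knowledge of when the event happened. The listed outcomes are scores, laboratory values, a fitness measure and a status at a visit (HAND prevalence). None of them supplies an event time.

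An analyst who followed Statistical Methods literally would have to invent an event. An ordinary Cox model would then treat scheduled visit dates as event times. An analyst who followed the Abstract would report a risk ratio and a risk difference. Study Outcomes makes HAND prevalence a primary outcome, so its reported effect could depend on which part of the article was followed, and the choice could be made after the data are seen.

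**Working it through.** **1. Does any listed outcome carry an event time?**

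| Outcome | Where listed | Type |
|---|---|---|
| Neurocognitive/cognitive performance | both lists | score |
| HAND prevalence | Study Outcomes, primary | status at a visit |
| Viral load, CD4 count | Study Outcomes, primary | laboratory value |
| QoL, activity limitation, participation | Study Outcomes, secondary; Statistical Methods, primary | score |
| Maximum oxygen uptake | Study Outcomes, secondary | fitness measure |

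None does.

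**2. Could HAND supply the event?** Because participants must be "diagnosed with HAND and physically inactive", the proportion with HAND at baseline is 100% by design. Time to first HAND is therefore ruled out. Remission or worsening could be events, but the article defines neither.

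**3. How finely would event times be known?** Study Outcomes gives baseline and two later visits. The text of Participant Timeline mentions only the assessment after the 12-week programme, and Figure 1 is not shown. Two post-baseline looks is therefore the most the text supports. A change of state would be known only to lie between consecutive visits, and all events would be tied at one or two dates.

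**4. Does the sample size rest on a hazard ratio?** It does not. The stated inputs are a difference in means of 13.4, SD 16.67, two-sided 5% and 90% power.

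- Normal approximation: n per arm = 2 × (1.960 + 1.282)² × 16.67² / 13.4² ≈ 32.5, rounded up to 33 (66 in total).
- Exact two-sample t calculation: 33.51, rounded up to 34 per arm (68 in total), with power 0.904.

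The stated 68 reproduces as a comparison of means, with no events, hazard ratio or follow-up time in it.

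**5. Would the two effect measures give the same number?** The article gives no event rates, so these are assumed pairs for illustration. Let p0 and p1 be the proportions of controls and exercisers who no longer meet HAND criteria at 12 weeks.

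- Risk ratio for remission = p1/p0
- Risk ratio for still having HAND = (1 − p1)/(1 − p0)
- Risk difference = p1 − p0, and NNT = 1/(p1 − p0)
- Grouped-time hazard ratio for remission = ln(1 − p1)/ln(1 − p0)

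| p0 / p1 | RR, remission | RR, still HAND | Risk difference | NNT | Grouped-time HR | HR ÷ RR, remission |
|---|---|---|---|---|---|---|
| 10% / 30% | 3.0 | 0.78 | 20 points | 5 | 3.39 | 1.13 |
| 20% / 40% | 2.0 | 0.75 | 20 points | 5 | 2.29 | 1.14 |
| 20% / 50% | 2.5 | 0.63 | 30 points | 3.3 | 3.11 | 1.24 |
| 30% / 60% | 2.0 | 0.57 | 30 points | 3.3 | 2.57 | 1.28 |

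For example, at 20%/40%: ln(0.60)/ln(0.80) = (−0.511)/(−0.223) = 2.29.

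The second and fourth rows share a risk ratio of 2.0 but have hazard ratios of 2.29 and 2.57. With a single look, the hazard ratio is only a transformation of the two proportions, so it adds no information about timing.

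**The case against.** The other side has several fair points.

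- **Everyone having HAND does not rule out every event.** A reader might infer that no hazard ratio is possible. The documents do not support that. The Introduction says that people with HAND can progress to severe impairment, and the first objective concerns symptom severity. Worsening, or loss of HAND status, could be an event in this cohort. Only incident HAND is excluded.
- **Grouped data can yield a hazard ratio.** Calling the result uninterpretable would go too far, because a discrete-time (complementary log-log) model estimates a hazard ratio from visit-based data. Undefined and poorly suited to the schedule is the fair description.
- **The two effect measures are not shown to answer one question.** The Abstract ties its measures to HAND. Statistical Methods ties hazard ratios to the intervention's effect over time, names no outcome, and places the sentence after a list of scores. A reader may infer two rival measures for one estimand, but the text does not say so. What it does show is that the Abstract's measures for HAND are absent from Statistical Methods and that the hazard ratio has no outcome attached.
- **The number of visits is uncertain.** The phrase about when variables are measured follows the list of confounders, so its reach is slightly ambiguous. A narrower reading leaves fewer looks, which does not help the hazard ratio.
- **An analysis plan that is not shown may define the event.** It may, and missing detail alone would be no finding. But the method stated here does not fit the outcomes stated here, and a separate plan would not remove that mismatch, or the mismatch with the Abstract, from this document.

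**Conclusion.** The hazard-ratio sentence is wrong as written. It commits the trial to an effect measure that none of its listed outcomes supplies, for an unnamed event, on a schedule of at most two post-baseline looks. The measures that the Abstract promises for HAND are not carried into Statistical Methods.

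The illustrated gap of 13% to 28% between hazard ratio and risk ratio rests on the assumed remission rates and on a single 12-week look. It shows that the measures differ and does not predict the trial's result.

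A reader might go further and conclude that the trial's main analysis fails. The documents do not support this: the stated group comparison is the repeated-measures analysis, with covariance adjustment for confounders, and the sizing is a t test of means. The point should be fixed before analysis, but it concerns a secondary strand of the plan.

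**What to change.** Delete the hazard-ratio sentence from Statistical Methods and replace it with the Abstract's approach. For the proportion still meeting HAND criteria at 12 weeks, report the risk ratio and the risk difference with 95% CIs, and report the same at the assessment three months after the intervention. Effects over time on the scores stay with the repeated-measures or covariate-adjusted analysis already planned.

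If the investigators want to keep a hazard ratio, the text should name the event (for example remission or worsening), its time origin and the censoring rule, and specify a discrete-time model for grouped data instead of an ordinary Cox model.

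The cost is a few sentences of text and an entry through the article's own amendment route. No new data, visits or participants are needed. The Results section says that the analysis has not yet been carried out, so the change can still be made beforehand.
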